### Data Management and Monitoring

Personal data will be collected and processed within this study in accordance with applicable data protection regulations. All study data will be documented and archived in pseudonymized form using a secure electronic database (REDCap). Access to the database is restricted to authorized study personnel, who are formally bound by professional confidentiality and data protection obligations. The pseudonymization key linking study IDs to personal identifiers will be stored separately in a password-protected electronic file accessible only to designated, nonblinded members of the study team.

No formal interim analyses are planned. Given the short intervention period and the low-risk profile of the intervention, no predefined stopping rules have been established. In addition to this, given the relatively small sample size, the establishment of an independent Data Monitoring Committee is not considered necessary. Study conduct, data quality, and protocol adherence will be monitored internally by the study team. Any protocol deviations or safety-relevant events will be documented and reviewed by the principal investigator.

### Safety

To evaluate safety, adverse events will be systematically assessed from initiation of the intervention until hospital discharge (T1-Tx) by actively inquiring about and documenting any undesirable effects. The severity of each adverse event will be classified as mild, moderate, severe, or life-threatening. In addition, a causality assessment will be performed for each event and categorized as no relationship, possible relationship, probable relationship, or definite relationship to the study intervention. The total number of adverse events and the number and percentage of participants experiencing at least 1 adverse event will be summarized by group.

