### Participants

Eligible participants are (1) female patients (2) aged 18 years or older with (3) newly diagnosed breast cancer who are scheduled to undergo therapeutic breast surgery at Robert-Bosch Hospital following initial diagnosis—written informed consent is required prior to study participation (4).

Patients will be excluded if (1) they have been diagnosed with an anxiety disorder within the previous 12 months or (2) if, in the opinion of the principal investigator, a psychological or mental condition precludes safe or appropriate participation in the study. Including participants with a diagnosed anxiety disorder may have introduced substantial variability in anxiety response due to underlying psychopathology and/or ongoing treatment. As such, this could act as a confounding factor, influencing preoperative anxiety beyond the transient, situational anxiety associated with surgery and limiting the internal validity of our study. Additional exclusion criteria include (3) the use of hearing aids; (4) the presence of skin irritation, inflammation, or eczema of the ear; (5) pregnancy; (6) insufficient proficiency in the German language; (7) unwillingness to permit storage and processing of personal health data as required by the study protocol; (8) missing or incomplete informed consent; and (9) prior acupuncture treatment (including NADA auricular acupuncture or acupressure) within the previous 3 months. According to the German S3 guideline on breast cancer [29] and the AGO Breast Committee recommendations for early breast [30], therapeutic surgery is typically scheduled within 3 to 6 weeks after histological confirmation of the diagnosis or 3 to 6 weeks after completion of neoadjuvant systemic therapy when indicated. Patients are usually admitted on the day before or the morning of surgery. Perioperative care is delivered in accordance with institutional protocols, including preoperative assessment by the anesthesia team, general anesthesia, multimodal analgesia, and risk-adapted PONV prophylaxis. The typical length of hospital stay is 1 to 3 days for breast-conserving surgery and 3 to 5 days for mastectomy, with or without reconstruction. All patients enrolled in the study receive this standard care regardless of group allocation.

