The intervention will be initiated prior to surgery. After application, participants will be instructed to keep the patches in place for 5 consecutive days. They will be asked to manually stimulate by pressing or massaging each pellet 3 times daily for 1 minute until a mild pressure sensation is perceived. Adherence to the intervention will be assessed during daily visits by study personnel through verification of pellet placement and documentation of any adverse events. In case of detachment, pellets will be replaced as needed. Participants discharged before the end of the 5-day application period will be instructed to remove the patches themselves on the fifth day, in accordance with the written instructions provided at the start of the intervention. In addition, according to the predefined intervention procedure, pellets will be replaced after 5 days if the patients are not discharged before. Intervention fidelity will be ensured through delivery of the intervention exclusively by NADA-certified personnel (physicians, medical assistants, or nursing staff) who have received formal training in the NADA protocol. In Germany, NADA certification requires completion of 2 sequential courses provided by NADA Deutsche Sektion e.V. [39], a basic course (basic I) and a supervision and final course (basic II), together with documented practical applications. The certificate is valid for 5 years, after which a refresher course is required for renewal. Physicians may perform acupuncture independently, whereas other health care professionals apply the NADA protocol under medical delegation, for which the certificate serves as the formal qualification. Auricular acupressure according to the NADA protocol is a noninvasive and low-risk intervention.

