#### Control Group: Standard Care (CTRL)

Participants allocated to the control group will receive standard preoperative care according to institutional practice. No auricular acupressure will be administered prior to surgery. To promote fairness between study groups, participants in the control group will be offered NADA auricular acupressure after completion of the last study measurement on the day of hospital discharge.

No restrictions will be placed on standard hospital procedures in either study group during the study period.

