### Intervention Discontinuation and Adherence

The intervention will be discontinued in the event of adverse reactions, participant requests, or if continuation is deemed inappropriate by the investigator for medical or safety reasons. Participants may withdraw from the study at any time without providing a reason and without consequences for their medical care.

To promote adherence, participants in the intervention group will receive verbal and written instructions detailing instructions regarding acupressure point stimulation and behavioral recommendations during the intervention period. In addition, participants will receive daily visits from study personnel during their hospital stay to reinforce instructions, address questions, and monitor proper application of the auricular patches and safety.

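### Active adverse-event enquiry ends at discharge although early-discharged patients wear the pellets at home until day 5, so events during home wear may be under-counted in the NADA arm

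*Protocol article*

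**What the plan says.** Protocol article, Safety: "adverse events will be systematically assessed from initiation of the intervention until hospital discharge (T1-Tx", where the bracketed label runs from the visit before surgery to the last inpatient visit. Events are graded for severity and causality, then summarized by group as a total count and as the number and percentage of participants with at least one event.

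Intervention Group section: "The intervention will be initiated prior to surgery", and "participants will be instructed to keep the patches in place for 5 consecutive days". It adds: "Participants discharged before the end of the 5-day application period will be instructed to remove the patches themselves on the fifth day". Pellets that come off are replaced, and patients still in hospital after 5 days receive a new set.

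Participants section: "Patients are usually admitted on the day before or the morning of surgery", and "The typical length of hospital stay is 1 to 3 days for breast-conserving surgery and 3 to 5 days for mastectomy".

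Intervention Discontinuation and Adherence section: "participants will receive daily visits from study personnel during their hospital stay". These visits are where pellets and safety are checked.

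Control Group section: "participants in the control group will be offered NADA auricular acupressure after completion of the last study measurement on the day of hospital discharge".

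**The concern.** The plan fixes two end points that do not match. Exposure runs to the fifth day, if necessary at home. Active enquiry about harm runs only to discharge. The article states both, so this is not a detail left to a fuller document. The plan also expects home wear, because it gives self-removal instructions for it.

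At stake is whether the safety table describes the intervention as prescribed. Stopping enquiry early can miss events from the 5-day application but cannot add any, so any error in the NADA-arm counts is towards too few. The Outcomes section openly limits postoperative complications to the hospital stay, but neither the Safety section nor the limitations in the Discussion say the same for adverse events. A reader of the results could take the table as covering the whole wear period.

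**Working it through.** The plan gives no figure for adverse-event coverage, so there is none to reproduce. The check has two parts.

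**1. Does anything else in the article cover home wear?**
- Daily visits (Intervention Group; Intervention Discontinuation and Adherence): inpatients only.
- 3-month follow-up (Outcomes): described as asking about the start or use of other complementary therapies. No adverse-event item is mentioned.
- Data Management and Monitoring: safety-relevant events will be documented and reviewed, but no route for collecting them after discharge is given.
- Per-protocol definition (Data Analysis): adherence counts to the fourth subsequent day or discharge, whichever is first, so home wear is not checked there either.

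None of these closes the gap.

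**2. How many wear days are unobserved?**

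Inputs from the article: wear of 5 days; stay L of 1 to 3 days (breast-conserving surgery) or 3 to 5 days (mastectomy); admission the day before or the morning of surgery. Not given: the day of application, how a stay is counted, and the surgery mix.

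Formula: unobserved days = 5 − min(5, observed in-hospital wear days). The discharge day is counted as observed.

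Three counting conventions, each an assumption:
- A: wear starts on the first counted hospital day, so observed days = L.
- B: one further observed day, so observed days = L + 1. Application on the day of surgery with discharge on postoperative day L gives the same count.
- C: application the day before surgery and discharge on postoperative day L, so observed days = L + 2.

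| Convention | Breast-conserving, L = 1, 2, 3 | Mastectomy, L = 3, 4, 5 |
|---|---|---|
| A | 4, 3, 2 | 2, 1, 0 |
| B | 3, 2, 1 | 1, 0, 0 |
| C | 2, 1, 0 | 0, 0, 0 |

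The range is therefore 0 to 4 days of 5 (0 to 80%) after breast-conserving surgery and 0 to 2 of 5 (0 to 40%) after mastectomy.

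For the whole arm, 1:1 allocation of 66 gives 33 NADA participants and 33 × 5 = 165 planned wear days. Assume a breast-conserving share s of 50% to 80% and stays spread evenly over the stated ranges. The unobserved share is then s × (mean unobserved days, breast-conserving)/5 + (1 − s) × (mean unobserved days, mastectomy)/5.
- A: means 3 and 1. s = 0.5 gives 0.5 × 0.60 + 0.5 × 0.20 = 40% (66 days). s = 0.8 gives 0.8 × 0.60 + 0.2 × 0.20 = 52% (85.8 days).
- B: means 2 and 1/3. s = 0.5 gives 0.5 × 0.40 + 0.5 × 0.067 = 23% (38.5 days). s = 0.8 gives 0.8 × 0.40 + 0.2 × 0.067 = 33% (55 days).
- C: means 1 and 0. s = 0.5 gives 0.5 × 0.20 = 10% (16.5 days). s = 0.8 gives 0.8 × 0.20 = 16% (26.4 days).

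These are shares of exposure time, not of events. No event rate or time to onset is stated, so they cannot be turned into a number of missed events.

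**The case against.** The strongest case against runs as follows.

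- *No safety conclusion exists yet, and the window is openly stated.* This stands. A reader might infer that the trial will reach an unduly favourable safety conclusion. The documents do not support that. Low risk is stated as a premise in the intervention and monitoring sections and, in the Introduction, rests on earlier studies. The Discussion says only that the method could be a low-risk adjunct if it proves effective. What remains is possible under-ascertainment in a descriptive summary.
- *The size depends on an unstated application day and on the stay.* This stands. Quoting only discharge on postoperative day 1 (2 of 5 days under C, 3 of 5 under B) would be selective, because longer stays can leave nothing unobserved. Hence the range that includes 0.
- *Later wear days need not carry more events.* This stands, since the article has no onset data. It does describe gold-coated pellets, exclusion of patients with ear skin problems and daily inpatient checks.
- *The two arms share a start.* A reader might infer that the by-group summary has no common start, because controls have no initiation of the intervention. But the T1 to Tx label applies to both arms. The wording is loose, no more.
- *Controls treated at discharge are wholly unobserved.* True of their exposure, but the offer is made for fairness and falls after the last inpatient measurement, outside the randomized comparison. It enters only an exploratory analysis of complementary therapy use.
- *Spontaneous reports after discharge are not excluded.* Also true, but spontaneous reporting is not the active enquiry that the Safety section promises for the inpatient days.

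None of this removes the mismatch between the wear period and the enquiry period.

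**Conclusion.** The point holds as a mismatch between the Safety and Intervention Group sections. As written, adverse events during home wear are not actively collected, and NADA-arm counts may be too low for the full prescribed exposure. The direction is certain; the size is not. Unobserved wear is 0 to 4 of 5 days after breast-conserving surgery and 0 to 2 of 5 after mastectomy. Over the arm it is roughly 10% to 52% of planned wear days, under the assumed 50% to 80% breast-conserving share, evenly spread stays and three counting conventions. The number of missed events cannot be computed and may be small. The primary outcome is measured at T1, before surgery, so it and the sample size of 66 are unaffected. This is worth correcting but does not threaten the trial's main result.

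**What to change.** Reconcile the two sections. End the adverse-event window at final patch removal or hospital discharge, whichever is later. Tie it to actual removal rather than to day 5, because pellets may be replaced after 5 days in patients still in hospital. Capture home days on a short self-report card (ear reactions, other events, date of removal) given with the written removal instructions that already exist.

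If that is not done, state in the Safety section and in the report that the safety summary covers in-hospital wear only.

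Optional: give the same card to controls who accept acupressure at discharge and tabulate them separately from the randomized comparison; and reword the start of the window so that it plainly applies to both arms.

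Cost: one extra form and a small amendment, with some cards not returned. Completion should be reported. Sample size and the primary analysis do not change. With 8 of 66 participants recruited at manuscript submission, an amendment at that point would have covered the remaining 58; how many it would cover now depends on recruitment since then.

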Several limitations must also be considered. Due to the nature of the intervention, blinding of participants and treating personnel is not feasible. This might introduce bias in the measurement of outcomes, particularly in the assessment of patient-reported outcomes such as anxiety and pain. To address this limitation, objective secondary outcomes, including medication use and postoperative complications, are assessed to provide clinically relevant endpoints less susceptible to reporting bias. Furthermore, the study does not include a sham control condition. The primary aim was to evaluate the efficacy of NADA auricular acupressure as an adjunct to routine care rather than to isolate specific acupoint-related effects. Consequently, the design does not allow differentiation between specific physiological effects of point stimulation and nonspecific effects related to expectation, therapeutic attention, or contextual influences. In addition, the sample size estimation was based on detecting a minimal clinically important difference in preoperative state anxiety as measured by the STAI-S. The study is therefore adequately powered for the primary endpoint but is not specifically powered to detect statistically significant differences in secondary outcomes. These should be considered exploratory, and effect estimates and corresponding CIs will be reported to facilitate interpretation of the magnitude and precision of observed differences.

Despite these limitations, the study addresses an important gap in the field of integrative oncology. There is growing interest among patients and health care providers in nonpharmacological strategies to improve perioperative well-being. However, integration of such approaches into clinical practice requires evidence from rigorously designed randomized trials. If NADA auricular acupressure proves effective in reducing perioperative anxiety and pain, it could represent a low-risk, low-cost, and easy-to-implement adjunct to standard care. Conversely, if no significant benefit is observed, the study will still provide important evidence to reconsider current assumptions regarding the role of auricular acupressure in perioperative oncology. Additionally, it will provide valuable information regarding effect sizes and variability in this patient population, thereby informing the planning of following studies.

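### Adverse-event capture ends at hospital discharge, but many NADA patients will go home wearing pellets until day 5, so part of the planned wear period has no described safety follow-up

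*Protocol article*

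**What the plan says.** In the Safety section, "adverse events will be systematically assessed from initiation of the intervention until hospital discharge (T1-Tx". Events are then summarized by group, as a total and as the number and percentage of participants with at least one.

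The section on the NADA intervention group sets the wear period: "participants will be instructed to keep the patches in place for 5 consecutive days", with each pellet pressed three times a day. It provides for early discharge: "Participants discharged before the end of the 5-day application period will be instructed to remove the patches themselves on the fifth day". For patients still in hospital after 5 days, the pellets are replaced.

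The same section gives the route by which events are recorded: "Adherence to the intervention will be assessed during daily visits by study personnel through verification of pellet placement and documentation of any adverse events". Intervention Discontinuation and Adherence places those visits in hospital: "participants will receive daily visits from study personnel during their hospital stay".

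Under Participants, "The typical length of hospital stay is 1 to 3 days for breast-conserving surgery and 3 to 5 days for mastectomy", and admission is usually on the day before surgery or that morning.

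For the control group, "participants in the control group will be offered NADA auricular acupressure after completion of the last study measurement on the day of hospital discharge".

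**The concern.** The safety window and the wear period have different ends. One closes at discharge, the other on day 5. Whenever discharge comes first, the remaining days of wear and self-stimulation have no described adverse-event capture. The stated stays make this the ordinary course after breast-conserving surgery, which is one of the two randomization strata.

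The days lost are always the last ones. It is plausible that skin or adhesive reactions build up with wear, although the article gives no data on this. An event that first appears at home cannot enter the reported counts under the rule as written. What is at stake is how complete the trial's safety information on the pellets will be. The primary outcome is measured before surgery and is not affected.

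**Working it through.** The plan states no figure for this, so there is none to reproduce. The check compares the two windows and counts pellet-days.

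**Inputs from the article**
- Planned wear: 5 days (NADA intervention group).
- End of adverse-event capture: discharge (Safety).
- Length of stay L: 1-3 days for breast-conserving surgery, 3-5 days for mastectomy (Participants).

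**Assumptions, because the article does not give them**
- In-hospital pellet-days equal L, or L + 1 if pellets go on one day earlier. The article says only that the intervention starts before surgery.
- The breast-conserving share p is 50-80%.
- Stays in the two strata are both at the short end, both mid-range or both at the long end.

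**Step 1: per patient.** Unobserved share = max(0, 5 − in-hospital pellet-days) / 5.

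| Surgery | L | Pellet-days = L | Pellet-days = L + 1 |
|---|---|---|---|
| Breast-conserving | 1 | 4/5 = 80% | 3/5 = 60% |
| Breast-conserving | 2 | 3/5 = 60% | 2/5 = 40% |
| Breast-conserving | 3 | 2/5 = 40% | 1/5 = 20% |
| Mastectomy | 3 | 2/5 = 40% | 1/5 = 20% |
| Mastectomy | 4 | 1/5 = 20% | 0% |
| Mastectomy | 5 | 0% | 0% |

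**Step 2: NADA arm.** Arm share = p × (breast-conserving share unobserved) + (1 − p) × (mastectomy share unobserved).

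| Stays (breast-conserving, mastectomy) | Pellet-days = L, p = 0.5 to 0.8 | Pellet-days = L + 1, p = 0.5 to 0.8 |
|---|---|---|
| 1 and 3 days | 60% to 72% | 40% to 52% |
| 2 and 4 days | 40% to 52% | 20% to 32% |
| 3 and 5 days | 20% to 32% | 10% to 16% |

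The two extremes are:
- highest: 0.8 × 0.80 + 0.2 × 0.40 = 0.72
- lowest: 0.5 × 0.20 + 0.5 × 0 = 0.10

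**Step 3: does another section close the gap?**
- Daily visits, where events are documented, take place during the hospital stay.
- The only later contact described is the 3-month follow-up, and its described content is a questionnaire on complementary therapies.
- Data Management and Monitoring says that safety-relevant events will be documented and reviewed by the principal investigator, but gives no way of collecting them after discharge.

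None of these supplies a capture route between discharge and day 5.

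**Step 4: controls.** Pellets are offered after the last in-hospital measurement, so any accepted exposure lies wholly outside the window. Uptake and wear time are not stated, so I put no number of pellet-days on it.

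**The case against.** The strongest reply is that discharge is a clear cut-off, the same in both arms, and gives a clean by-group comparison. The outcomes text openly adopts an in-hospital window for surgical complications because stays are short. This stands as a defence of the by-group comparison, which should be left alone. It does not supply the missing information on pellets worn at home, and the article states its caveat about later onset for surgical complications only.

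It is also fair to say that the size is uncertain. The surgery mix, the time of placement and the distribution of stays are all assumed. A single mid-range figure such as 40-52% would suggest more precision than the inputs allow. Patients who stay 5 days or more are covered for the whole of their first application.

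A reader might infer several stronger things that the article does not support:
- *The unobserved control exposure biases the arm comparison.* It does not. The offer is voluntary and comes after the last in-hospital measurement, so the comparison up to discharge is unaffected.
- *The adverse-event percentages necessarily understate harm.* They miss only events that first arise after discharge. The article gives no event rate from which to size this.
- *The plan will conclude low risk from these data.* The Discussion is conditional on effectiveness when it says "it could represent a low-risk, low-cost, and easy-to-implement adjunct to standard care". Elsewhere, low risk is stated as a prior property of the intervention.
- *Nobody will check that pellets come off.* The article describes no check, but the written patient instructions are not shown and may contain one.

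**Conclusion.** The mismatch is real and follows from the article's own rules: capture stops at discharge, while planned wear goes on at home until day 5. For a breast-conserving patient, 40-80% of pellet-days are unobserved if pellet-days equal length of stay, and 20-60% if pellets go on a day earlier. For the NADA arm the range is about 10-72%, given the assumed 50-80% breast-conserving share. Even the most favourable of these scenarios leaves some wear unobserved.

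The consequence is incomplete descriptive safety data on the pellets, including any that controls accept at discharge. It is neither a bias in the randomized adverse-event comparison nor a threat to the efficacy results.

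**What to change.** Keep the by-group adverse-event comparison up to discharge unchanged. Add the following to it:

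1. For anyone wearing pellets, extend adverse-event capture to the later of discharge or removal of the last pellet set. The wording must include sets re-applied in patients still in hospital after 5 days. A window that simply ended at the first removal would cut those patients off earlier than the present rule does.
2. At discharge, give every participant who leaves with pellets, in either arm, a short card asking for ear symptoms and the date of removal. Attaching it only to the intervention group's instructions would miss the controls who accept the offer.
3. Add one item on ear problems to the 3-month questionnaire in both arms, as a back-up for cards not returned.
4. Report these post-discharge events descriptively by exposure, outside the randomized comparison, with events in controls shown separately.
5. Limit any safety statement to the wear time actually observed.

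The cost is one card, one questionnaire item and a wording amendment, with no additional visits. Some cards will not come back, and the 3-month item will carry recall error. At manuscript submission 8 of 66 participants had been recruited, so 66 − 8 = 58 were still to come. The number who can still be covered depends on how soon the amendment is made.
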